### Causal mediation analysis

Although the ITT analysis will provide the estimated overall effect of INSPIRE on PEG scores, we will conduct a secondary analysis to understand the pathways of effect for INSPIRE to improve PEG scores around or through intermediate variables using mediation analyses [123–125]. Specifically, a generalized linear model will be fitted for mediators at follow-ups as the outcome and the intervention (INSPIRE vs. control) as the predictor, and then another linear model will be fitted for the outcome PEG reduction over 12 months on the intervention (INSPIRE), mediators, and intervention*mediator interactions with relevant baseline covariates included in the models. Based on the quasi-Bayesian Monte Carlo approximation, estimates from the models will be used to compute the direct and indirect (mediation) effects of the intervention around and through the mediators on CP management [126]. A significant mediation effect will indicate an INSPIRE-mediator-PEG score pathway.

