### Sample size justification

The sample size calculation was based on the primary analysis comparing the primary outcome (PEG scores) between the INSPIRE and control groups at 3 months. Based on the literature, we expect to observe an effect size of 0.3 in PEG score at 3 months [57, 58, 60, 70, 119, 120]. With a power of 0.8 and Type I error of 0.05 in a two-sided independent t-test, assuming 73% retention, a sample size of 586 (293/group) is needed at the enrollment to identify such an effect size at 3 months.

Although we will use Holm’s step-down procedure to adjust for multiple comparisons in secondary analyses, we will take a conservative approach in the power calculation for secondary analyses using Bonferroni with an individual Type I error of 0.01 to control for the family-wise Type I error in 5 comparisons on secondary outcomes. The sample size of 586 (293/group) at the enrollment will provide a power of 0.8 to detect an effect size of 0.366 (a group difference of 0.366*SD) in secondary outcomes between the INSPIRE and control groups. We consider the detectable effect sizes realistic that we expect to observe in the study. With a less conservative Holm’s step-down approach than Bonferroni that we will use in actual secondary analyses to adjust for multiple comparisons, the planned sample size will detect a smaller effect size than 0.366 with a power of 0.80 for secondary outcomes. Adverse events, severe adverse events, and unanticipated problems during the study will be summarized with frequencies and percentages and compared between the treatment groups using Fisher’s exact test or Chi-squared test as appropriate.

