### Primary analysis of the primary endpoint

Our primary analyses will assess the intention-to-treat (ITT) effect of INSPIRE on PEG score compared to the control group at 3 months. The ITT approach will include all the randomized participants, including non-adherers and dropouts, in the analyses. A linear mixed effects model (LMM) will evaluate the group difference over time in change in PEG scores. The models will include the stratification variable (language), group (INSPIRE vs. control), time, and time*group interaction as fixed effects, and random intercept and slope for the nested three-level random effects controlling for correlation due to clustering by clinics, providers, and participants. Baseline demographics and characteristics will be balanced between the two groups by randomization; if any baseline covariates are identified as imbalanced, these will also be included in models. Time will be included in the LMM in an appropriate way (linear, categorical, quadratic, or two pieces) based on the graph of the outcome over time. The time*group interaction will provide the estimated ITT effect of INSPIRE compared to control over time, where the contrast between the INSPIRE and control groups at 3 months is our primary interest, using a significance level of 0.05. The LMM adopts a less stringent assumption on missingness (i.e., missing at random) than complete case approaches (missing completely at random) and will include all available data from all the randomized participants in the analysis.

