### Secondary analyses of the primary outcome

Secondary analyses of PEG scores will supplement the primary analysis, including (1) a modified intention-to-treat (mITT) analysis will be performed using the same LMM as the primary analysis but excluding randomized participants who do not participate and drop out after Week 0 and those who do not have chronic pain or have PEG<4 and drop out by Week 1; (2) using an independent *t* test to test corresponding contrasts from the same LMM as the primary analysis to assess if PEG score would be different between the treatment groups at 6 and 12 m; (3) using potential outcome-based approaches to estimate the INSPIRE effects while accounting for nonadherence to intervention [121]; (4) assessing if there are any baseline covariates associated with dropouts and performing sensitivity analyses to see how much the results will change after including covariates associated with dropouts in the models, using multiple imputation, or considering pattern mixture models; and (5) exploring potential heterogeneous effects by demographics or characteristics with sub group analyses. Given the discovery feature of those secondary analyses, a significance level of 0.05 will be used to avoid missing potentially important findings, which will be verified in future studies.

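### As written, the mediation models default to participants with a month-12 PEG score, and the plan's multiple imputation is not extended to them

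*Protocol article*

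**What the plan says.** The Causal mediation analysis section names two models. First, "a generalized linear model will be fitted for mediators at follow-ups as the outcome and the intervention (INSPIRE vs. control) as the predictor". Second, "another linear model will be fitted for the outcome PEG reduction over 12 months on the intervention (INSPIRE), mediators, and intervention*mediator interactions". The only covariates it names are baseline ones. The effects are derived from those fits: "Based on the quasi-Bayesian Monte Carlo approximation, estimates from the models will be used to compute the direct and indirect (mediation) effects". No random effect, repeated-measures structure, follow-up PEG covariate or missing-data method is named.

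The primary analysis is handled differently. It uses a linear mixed model that "will include all available data from all the randomized participants in the analysis", and the article gives the reason: "The LMM adopts a less stringent assumption on missingness (i.e., missing at random) than complete case approaches (missing completely at random"). The Analysis of secondary endpoints section uses generalized linear mixed models of the same kind.

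Item 4 under Secondary analyses of the primary outcome provides for "performing sensitivity analyses to see how much the results will change after including covariates associated with dropouts in the models, using multiple imputation", or pattern mixture models. That list concerns the treatment effect on PEG scores, and nothing carries it over to mediation.

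The only retention figure is in the Sample size justification: "assuming 73% retention, a sample size of 586 (293/group) is needed at the enrollment". It belongs to a calculation for month 3. No month-12 figure is given.

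**The concern.** The article gives a reason for preferring mixed models and then leaves that family for the mediation analysis without saying how missing data are handled there. A plain linear model on a 12-month change uses only people with a month-12 PEG, and PEG at 3 and 6 months, which may well predict who leaves, plays no part in it.

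Arm-dependent dropout is credible. One arm has twelve weekly coaching calls plus boosters, and the coaches also work on obstacles to completing surveys. The other arm has one orientation visit. If staying depends on arm and on how pain has changed, selecting those who stayed disturbs the randomised comparison that the mediation models rely on. The section reads a significant mediation effect as evidence of a pathway. That reading might then describe those who stayed rather than those randomised.

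**Working it through.** **1. The models side by side.**

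| Analysis | Model | Data used | Missing-data method |
|---|---|---|---|
| Primary (PEG) | linear mixed model | all available visits | missing at random; imputation and pattern mixture as sensitivity |
| Secondary endpoints | generalized linear mixed models | repeated visits | same model family |
| Mediation | generalized linear model, then linear model | 12-month PEG reduction, baseline covariates | none named |

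**2. Who contributes.** PEG and the primary mediators are scheduled at baseline and months 3, 6 and 12 (Table 1). Someone seen at months 3 and 6 but not at 12 informs the primary model and not the mediation outcome model. Social isolation, internalized stigma and healthcare trust are scheduled only at baseline and month 12, so for these an early leaver lacks both the mediator and the outcome.

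**3. How many.** First, the plan's own figure. For an effect size of 0.3, two-sided alpha 0.05 and power 0.80, the t-test needs 176 per group. Then 176/0.73 = 241.1, or 242 per group and 484 in total, not 586. The stated 293 per group matches about 60% retention (176/0.60 = 293.3). So does the stated 0.366 detectable effect at alpha 0.01, which is 0.3662 at 60% and 0.332 at 73%. That mismatch is a separate matter, but it means that even the month-3 retention is uncertain. For month 12 only a range can be shown (retention assumed, 586 enrolled):

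| Month-12 retention | With outcome | Without |
|---|---|---|
| 50% | 293 | 293 |
| 60% | 352 | 234 |
| 73% | 428 | 158 |
| 80% | 469 | 117 |

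**4. Bias.** Simulation with N = 400,000; every effect is assumed.

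- Baseline PEG: mean 6, SD 1.8.
- Mediator = 0.4·arm + 0.1·(baseline − 6) + noise (SD 1).
- PEG at 3 months = baseline − 0.3·arm − 0.6·mediator + u + noise.
- PEG at 12 months = baseline − 0.2·arm − 0.6·mediator + u + noise. The term u is shared by both visits; u and each noise term have SD 1.
- Indirect effect = (arm coefficient in the mediator model) × (mediator coefficient + half the interaction coefficient). The true value is 0.4 × 0.6 = 0.24.
- Dropout is logistic, tuned to 60% or 73% retention. Relative bias = estimate/full-data value − 1, for example 0.296/0.240 − 1 = +23%.

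| Dropout depends on | Retention | Full data | Completers in both models | Mediator model on all, outcome model on completers |
|---|---|---|---|---|
| nothing | 60% | 0.239 | 0.242 | 0.239 |
| nothing | 73% | 0.240 | 0.239 | 0.240 |
| arm, mediator, baseline PEG | 60% | 0.240 | 0.263 (+10%) | 0.241 |
| arm, mediator, baseline PEG | 73% | 0.240 | 0.261 (+9%) | 0.240 |
| 3-month PEG | 60% | 0.242 | 0.223 (−8%) | 0.231 (−5%) |
| 3-month PEG | 73% | 0.242 | 0.228 (−6%) | 0.235 (−3%) |
| 3-month PEG, one arm only | 60% | 0.240 | 0.296 (+23%) | 0.234 (−2.5%) |
| 3-month PEG, one arm only | 73% | 0.243 | 0.286 (+18%) | 0.238 (−2%) |
| month-12 PEG itself | 60% | 0.241 | 0.213 (−12%) | 0.221 (−8%) |
| month-12 PEG itself | 73% | 0.240 | 0.219 (−9%) | 0.224 (−7%) |

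A second set of assumed effects (true value about 0.17, retention about 60–62%) gave these completer against full-data values:

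- random dropout: 0.171 against 0.171;
- dependence on 3-month PEG, equal in both arms: 0.166 against 0.172 (−3%);
- the same with retention of 69% and 54% by arm: 0.150 against 0.171 (−12%);
- dependence on 3-month PEG that differs by arm: 0.121 against 0.173 (−30%).

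Where the dependence on 3-month PEG differs by arm, the two set-ups err in opposite directions.

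**5. Does the fix work?** In the first set-up, imputing the missing 12-month reduction by arm from baseline PEG, the mediator and 3-month PEG recovered the full-data value under every mechanism that depends only on observed data. When dropout depended on month-12 PEG itself, imputation reduced the error without removing it.

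**The case against.** The strongest reply is that this is silence, not error. The article condenses a fuller plan, and missing-data handling for a secondary mediation analysis is commonly left to a statistical analysis plan, which is not shown here. The same two models could be kept under imputation, so naming them does not commit the trial to complete cases. This stands in part. A reader might infer that early leavers are excluded, but the article never says so; it follows only from fitting the named models as they are described. The section is not silent on method, though: it specifies models that default to complete cases and does not link them to the imputation planned elsewhere.

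The wording about mediators at follow-ups and a reduction over 12 months might also cover several visits. That reading does not settle the matter, because a plain linear model would then treat repeated measures on one person as independent, whereas the other analyses model that correlation.

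The text also does not restrict the mediator model to people with a month-12 PEG. If all observed mediators are used, the bias in the table is smaller. That relief is not available for mediators measured only at baseline and month 12.

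Two further stronger readings are not supported. One is that the plan contradicts itself: the primary analysis section calls its missingness assumption less stringent, but does not rule out complete-case work elsewhere. The other is that bias would make the indirect effect too small: the direction changes with the assumed mechanism. Finally, participants who stop the intervention are still followed, so only those without month-12 data are affected.

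**Conclusion.** The point holds in a limited form. Fitted as described, the mediation models use people with a month-12 PEG, make no use of 3- and 6-month PEG as predictors of dropout, and need a stronger missingness assumption than the mixed models used for the other endpoints. Bias arises if dropout depends on post-baseline PEG and differs by arm, and it can go either way. In the assumed scenarios it ran from none under random dropout, through 3% to 8% when dependence on 3-month PEG was the same in both arms, to −30% or +23% when that dependence differed by arm. These figures illustrate the mechanism and do not predict the trial's bias, since neither 12-month retention nor the reasons for dropout are known. The analysis is secondary and the primary result is untouched, so the point is minor.

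**What to change.** In the Causal mediation analysis section, state that both models are fitted in multiply imputed data and the results pooled. Impute separately by arm, with baseline, 3- and 6-month PEG and the mediators in the imputation model. Alternatively, weight participants with month-12 data by the inverse probability of remaining, given arm and PEG at 3 and 6 months. Keep the completer fit as a sensitivity check. The timing of mediators and outcome need not change.

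The cost is a sentence or two in the plan and modest extra programming; no new data and no change to conduct are needed. The remaining weakness is reliance on missing at random. For the mediators measured only at baseline and month 12, the imputation has less to draw on, because no interim value of the mediator exists.

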#### Participant randomization

We will randomize at the level of the patient. While this poses a modest risk of provider contamination between intervention and control participants, providers will not receive any communication from the study team after enrollment. We have further addressed the potential effect of contamination by increasing sample size, allowing detection of smaller intervention effects.

Participants will be stratified by 4 demographic groups (Cantonese-speaking, Spanish-speaking, Black/African American English-speaking, and multi-cultural English-speaking) and randomly assigned 1:1 to either the INSPIRE intervention (Group 1) or control groups (Group 2). The CRC will utilize random block randomization to maximize balance between treatment groups throughout accrual while ensuring the randomization sequence remains unpredictable. A random allocation sequence was generated using a computer, where treatment groups were labeled as Group 1 or 2. After participants consent to study participation and complete baseline measures, clinical research coordinators will assign the next available study ID number in sequence, identify the allocated group, and inform participants of their assignment. The study ID number and Personal Health Information (PHI) will be stored in a HIPAA-compliant manner (REDCap) along with the intervention assignment (Group 1 or 2). Study personnel responsible for outcome evaluations will be blinded to which Group 1 or 2 represents.

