#### Mediators and common factors

Primary mediators (i.e., variables most directly linking the intervention with desired outcomes) will be assessed at timepoints listed in Table 1 and will include pain cognitions (catastrophizing, psychological flexibility, pain self-efficacy) and health behavior (behavioral activation, exercise, movement, sleep) [88–91]. Secondary mediators (i.e., variables that indirectly exert influence on outcomes) include stigma and isolation, trust in healthcare, engagement, and satisfaction with the INSPIRE intervention [92–95]. The hypothesized INSPIRE Treatment Effects Pathway Model is described in Fig. 3.

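### The mediation section treats a significant indirect effect alone as a pathway, so a mediator that INSPIRE changes and that shares an unadjusted cause with PEG can be declared one without affecting PEG

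*Protocol article*

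**What the plan says.** The protocol article, under Causal mediation analysis, sets out two regressions. In the first, "a generalized linear model will be fitted for mediators at follow-ups as the outcome and the intervention (INSPIRE vs. control) as the predictor". In the second, "another linear model will be fitted for the outcome PEG reduction over 12 months on the intervention (INSPIRE), mediators, and intervention*mediator interactions". Adjustment is described only as "with relevant baseline covariates included in the models". The effects are then derived: "Based on the quasi-Bayesian Monte Carlo approximation, estimates from the models will be used to compute the direct and indirect (mediation) effects". The section ends with the interpretation rule: "A significant mediation effect will indicate an INSPIRE-mediator-PEG score pathway".

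Under Participant randomization, patients are "randomly assigned 1:1 to either the INSPIRE intervention (Group 1) or control groups (Group 2"; nothing else is randomised. Under Mediators and common factors, the primary mediators are listed as "pain cognitions (catastrophizing, psychological flexibility, pain self-efficacy) and health behavior (behavioral activation, exercise, movement, sleep".

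**The concern.** An indirect effect is the product of two links. The link from arm to mediator is protected by randomisation. The link from mediator to PEG is not: it is an association within arms, and it is causal only if no unadjusted factor drives both. Baseline covariates deal with what was measured at baseline. They cannot deal with unmeasured causes or with causes that arise during follow-up. The closing rule makes no allowance for this, and it stands under a heading that calls the analysis causal.

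Several features of the design make a shared cause plausible:

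- Participants know their arm (Blinding).
- PEG and the mediator scales are self-reported in the same surveys, so mood or reporting style could move both.
- INSPIRE also aims to change depression and anxiety, which could act on a mediator and on PEG.
- Table 1 schedules stigma, isolation and trust only at baseline and 12 months, while the outcome is the change in PEG over 12 months. For these three, time order gives no protection.

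The coaching modules in Table 2 target catastrophizing, self-efficacy, flexibility and isolation. A shift in those scales is thus what the trial itself expects. At stake are the mediator conclusions, which the Objective and Trial design sections name among the trial's aims.

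**Working it through.** The mediation section states no figure of its own, so there is none to reproduce. The check asks how often the stated rule declares a pathway for a mediator that has no effect on PEG.

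**Inputs**

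- Analysed per arm, n: 214 is 73% of 293 (0.73 × 293 = 213.9), from Sample size justification. 176 is the two-sided t-test size for 0.3 SD at 80% power and alpha 0.05. Both relate to 3 months; the article gives no 12-month retention.
- Effect of INSPIRE on the mediator, a: not in the documents. Assumed 0, 0.1, 0.2 or 0.3 SD.
- Residual mediator-PEG correlation from an unadjusted cause, rho: not in the documents. Assumed 0.1, 0.2 or 0.3.
- True effect of the mediator on PEG: 0. Direct effect of the arm on PEG: 0.3 SD.

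**Bias.** Write M = a·T + e_M and Y = 0.3·T + e_Y, with unit residual SDs and corr(e_M, e_Y) = rho. Regressing Y on T and M gives M a coefficient that tends to rho rather than 0. The estimated indirect effect therefore tends to a × rho. With a = 0.3 and rho = 0.3 that is 0.09 SD; the simulated mean is 0.092. The bias does not shrink with more patients.

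**Approximate rate of a false pathway.** The rule fires roughly when both links are significant:

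- z_a = a / √(2/n)
- z_b = rho / √((1 − rho²)/(2n))
- rate ≈ P(|Z_a| > 1.96) × P(|Z_b| > 1.96)

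For n = 214, a = 0.3, rho = 0.2: z_a = 0.3/0.0967 = 3.10, probability 0.874; z_b = 0.2/0.0474 = 4.22, probability 0.988; product 0.863. For n = 176: z_a = 2.81 (0.804), z_b = 3.83 (0.969); product 0.779.

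**Simulation of the stated procedure.** Linear mediator model; linear outcome model with the arm-by-mediator interaction; 1,000 quasi-Bayesian draws; 95% interval for the average indirect effect; 2,000 trials per cell. Percentage of trials declaring a pathway:

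| Shift a (SD) | n per arm | rho 0.1 | rho 0.2 | rho 0.3 |
|---|---|---|---|---|
| 0 | 176 | 1.8 | 4.7 | 5.0 |
| 0 | 214 | 2.2 | 4.3 | 6.0 |
| 0.1 | 176 | 6.4 | 14.7 | 16.6 |
| 0.1 | 214 | 8.7 | 17.7 | 19.5 |
| 0.2 | 176 | 18.8 | 42.8 | 44.6 |
| 0.2 | 214 | 25.8 | 52.1 | 53.8 |
| 0.3 | 176 | 36.4 | 77.8 | 82.6 |
| 0.3 | 214 | 45.0 | 86.2 | 88.3 |

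The simulated 86.2% and 77.8% agree with the hand approximations of 86.3% and 77.9%. Independent repeats differ by a few points, hence the rounded ranges in the conclusion. If 12-month losses left only 150 per arm, the row for a = 0.3 would read about 27%, 67% and 74%. With no unadjusted cause (rho = 0) at 214 per arm, the rate is at most about 6% for every shift examined, up to 0.5 SD.

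**The case against.** **A reader might infer that any mediator correlated with PEG will usually be declared a pathway.** The figures do not support that. INSPIRE must also move the mediator. If it does not, the rate stays near or below 5%; at 0.1 SD it is at most about 20%. At 0.3 SD with rho = 0.1 a false pathway is still not the majority result.

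**A reader might infer that the protocol's own definitions prove uncontrolled common causes.** The text says "Secondary mediators (i.e., variables that indirectly exert influence on outcomes". A variable that reaches PEG only through a primary mediator does not confound that mediator: in a simulated chain of this kind the mediator coefficient was 0.398 against a true 0.40. If the second route runs through another primary mediator, entering both removes the distortion (0.083 alone, 0.000 jointly), and the outcome model does name mediators in the plural. The pathway figure that might settle this is not shown. Uncontrolled common causes are plausible here, but not documented.

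**A sensitivity analysis and a covariate list belong in the analysis plan.** This is correct, and their absence from an article is not the point. The point is a rule that the article does state. No other section softens it: the sensitivity analyses under Secondary analyses of the primary outcome concern dropout, the remark there about verification in future studies covers the PEG analyses listed in that section, and the limitations in the Discussion do not mention mediator confounding.

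**The stakes are limited.** This also stands. The analysis is labelled secondary, the Objective and Discussion speak of potential mediators, and the primary comparison is unaffected.

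**Conclusion.** The concern holds in a conditional form. The rule converts significance into a causal statement that the design does not secure. A mediator that INSPIRE changes and that shares an unadjusted cause with PEG can be declared a pathway while having no effect on PEG.

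For a 0.3 SD shift and 176 to 214 analysed per arm, this happens in about 35% to 46% of trials at a residual correlation of 0.1, and about 75% to 88% at 0.2 to 0.3. It falls to about 45% to 55% at a 0.2 SD shift (correlation 0.2 to 0.3), about 6% to 20% at 0.1 SD (correlation 0.1 to 0.3), and about 5% or less with no shift.

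These rates depend on the assumed shift and correlation, neither of which the documents give, and on 3-month numbers applied to a 12-month outcome. That the rule overstates what significance shows does not depend on them.

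**What to change.** Replace the last sentence of Causal mediation analysis with:

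> A significant indirect effect will be reported as consistent with an INSPIRE-mediator-PEG pathway under the assumption of no unmeasured mediator-outcome confounding; for each mediator the error correlation at which the indirect effect reaches zero will be reported alongside it.

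State that baseline PEG and the baseline value of the mediator, where collected, enter both models. The present wording may already intend this; if so, it only needs saying. Engagement and the app rating have no baseline value.

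Do not add a fixed pass mark, such as requiring the sign to hold up to an error correlation of 0.3. In the linear case without interaction, that amounts to requiring a mediator-PEG correlation within arms above 0.3. In simulations with no confounding and a genuine standardised effect of 0.25, only about 8% to 16% of trials met it, so most real pathways of moderate size would be discarded.

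The cost is a little more analysis within the framework already chosen and more cautious mediator claims. No new data, visits or patients are needed.
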